Several studies (Coleman et al., 2015; Hustad et al., 2018; Pennington et al., 2020; Tan et al., 2020) have attempted to explore demographic variables, early clinical characteristics, and environmental factors in predicting communication ability in children with CP at school entry. Studies have demonstrated that communication, cognition, and motor performance at an early age are critical for predicting future functional communication in children with CP (Coleman et al., 2015; Hustad et al., 2018; Pennington et al., 2020; Tan et al., 2020). However, most standardized tests require behavioral repertoires that exceed the capabilities of young children with CP, which makes these measures too difficult to use to assess these children reliably (Geytenbeek et al., 2010; Nordberg, 2018). Other non-standardized tests, such as parent-completed measures and grade-level classification systems, are unlikely to easily and adequately capture the scope of information necessary to track impairment-related changes (Geytenbeek et al., 2010; Potter, 2016). All these limitations make these methods less accurate in identifying or predicting children with CP at high risk for communication impairment.

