#### Sample Size

There are no directly available data to assess the relationship between connectome-based features and clinical assessments of children with BCP to predict their communication ability at school entry. The sample size was calculated according to a previous study (Coleman et al., 2016). In that study of children with CP with a total sample size of *n* = 131, the number of children with communication abnormalities was 62 (47.0%). Multiple linear regression showed that lesion type and five semiquantitative indices that reflected the severity of brain lesions were related to the communication assessment score. However, the efficient size f2 cannot be directly calculated because the R2 and residual variance in the multiple regression model were not reported in the study (Coleman et al., 2016). Geytenbeek et al. (2015) used multiple linear regression based on MRI measures to evaluate language comprehension in non-speaking children with severe CP and PWMLs; that study revealed that the R2 of the model was 0.36. Choi et al. (2017) also found significant negative relationships between the severity of PWMLs and expressive language and between the severity of PWMLs and receiving language performance. Although the above results indicate that the MRI measures could be used to adequately predict communication performance in children with CP, we still assumed a lower efficient size for the MRI measures (f2 as 0.10) to ensure a sufficient sample size for an accurate prediction of communication performance in children with CP. Based on previous studies (Geytenbeek et al., 2015; Coleman et al., 2016; Choi et al., 2017), the number of predictors was set as 6. If α = 0.05, 1-β = 0.80, then the study requires enrollment of 143 participants according to the power calculation by G*Power, version 3.1.9 (Faul et al., 2009). According to previous follow-up experience and given a maximum anticipated dropout rate of 20%, a total sample size of 178 children with BCP and PWMLs will be needed.

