### Clinical Data Collection

#### Demographic Data

Basic demographic and clinical information will be collected from families and health records. The following general information will be collected: age at MRI examination, sex, body weight, height, medical history, comorbidities, epilepsy, family makeup, seizure history, and medication. In addition to the above information, prenatal factors have also been shown to be related to brain injury and affect language development outcomes. Thus, birth history variables, including delivery mode, gestational age, birth weight, head circumference, body length, and Apgar score, will also be documented.

Furthermore, a systematic review (Vaillant et al., 2020) indicated that the factors in some domains of the International Classification of Functioning, Disability and Health – Children and Youth framework are relevant for language comprehension in children with CP. According to this concept, children’s motor type, motor distribution, hand function (MACS), gross motor function (GMFCS), hearing function, visual function, speech function, socioeconomic status, parental educational level, parental occupation, and birth order will be recorded.

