### Models for Predicting Communication Impairment

#### Preselection of Predictive Features

Since the number of streamlines between two cortical regions is averaged, the connectivity matrix is symmetrical with respect to the diagonal, and only the lower triangular matrix will be used for further analyses. For both lesion-based and connectome-based analyses, the feature set will include hundreds to thousands of feature vectors, and such high-dimensional data can cause the “curse of dimensionality.” To reduce the number of potential features introduced into the predictive model, a preselection procedure will be performed to exclude noisy or uninformative predictors from being fed into the prediction model, which can reduce the chance of model overfitting. First, for lesion-based analyses, only gray matter regions that are lesioned in more than 10% of the patients will be entered into the analysis. Second, for the links in the connectome matrix-based analyses, only those that are present in more than 75% of the patients will be entered into the analysis. After the above steps, each subject will have three feature sets: the lesion feature set, connectome feature set, and combination feature set.

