Images from four sites (four hospitals) will be randomly partitioned into four equal portions. Approximately three-quarters of these images will be used as a “training cohort,” and the remaining one-quarter of these images will be used as a “test cohort.” In the “training cohort,” the proportion of lesioned voxels in the ROI and the links of the connectome matrix that are not shown difference between absence of communication impairment group and communication impairment group will be excluded, where the significance level is defined as *P* < 0.05 without multiple comparison correction in the two-sample test. The selected features will be used to define models predicting presence or absence of communication impairment in children with BCP. For each prediction model, 10-fold cross-validation (CV) will be used to evaluate the performance. This means that the “training cohort” will be divided into a training (nine folds) and a validation dataset (one fold), leaving 9 of 10 participants in the training dataset and the remaining participants in the testing dataset. For the training cohort, the various hyperparameters within each algorithm will be used to determine the prediction model. Then, the model will be applied to the validation dataset to predict children with the presence or absence of communication impairment (predicted label). The same procedure will be repeated with each of the one-fold participants or the left-out participants in the leave-one-out procedure, serving as the validation dataset for 10 iterations. Thus, each subject will receive a predicted label, and the accuracy of predictive model will be evaluate by comparing predicted labels to true labels of BCP children. The CV step will be repeated 100 times with random cohort designation to select the model with the best prediction accuracy. The whole “training cohort” will be reused in its entirety to retrain the model based on the classification algorithm and hyperparameters of the prior selected model. Then, the retrained model will be used to evaluate the “test cohort,” and the communication performance of every subject of the “test cohort” will be predicted by the model. The final accuracy of the prediction model will be defined by comparing predicted labels to true labels of BCP children in the “test cohort,” The Receiver Operating Characteristic (ROC) curve and the area under curve (AUC) will be calculated to evaluate the predictive ability of built models. A two-sided Hotelling-Williams test (Steiger, 1980) will be used to determine whether the multimodality prediction model is more accurate than any of the single-modality prediction models. *P* values < 0.05 will be considered indicative of statistically significant differences across models. Given the possible effects of age on imaging measures, the “test cohort” will be divided into three groups: younger (6–12 months), middle-aged (12–18 months), and elderly (18–24 months years), according to their age at MRI scan. The optimal model will be applied to all subgroups to exam whether the prediction accuracy changes with age at MRI scan.

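### Age at MRI enters no feature screen or model, and the only age check splits the test cohort into bands of about 12 to 15 children

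*Protocol article*

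**What the plan says.** Under Demographic Data the protocol lists scan age first among the variables recorded: "The following general information will be collected: age at MRI examination, sex, body weight". Study Procedures sets entry at corrected ages of 6 to 24 months.

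Preselection of Predictive Features then defines what the models may use: "each subject will have three feature sets: the lesion feature set, connectome feature set, and combination feature set". The Figure 2 legend builds one model from each set, and the combination set is lesion plus connectome. Under Development and Validation of Prediction Models, lesion proportions and connectome links are screened by an unadjusted two-sample test between outcome groups over the whole training cohort. Age is not part of that test, of model fitting or of the planned model comparison.

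The same section acknowledges that age may influence the imaging measures. Its response is to divide the test cohort into bands of 6–12, 12–18 and 18–24 months, so that 12 and 18 months each fall in two bands. Then: "The optimal model will be applied to all subgroups to exam whether the prediction accuracy changes with age at MRI scan".

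**The concern.** If age may affect the features, a check made after screening, tuning and model selection cannot take that effect out. Age-related variation stays in each feature when features are kept or dropped at P < 0.05, and when the classifiers are trained. Where age is unrelated to outcome, this widens the within-group spread and weakens real differences. Where age is related to outcome or case mix, it could also bias the features.

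The check is the only safeguard, and it is weak. A finding of no difference between bands would say little, but could be reported as evidence that accuracy does not depend on scan age.

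**Working it through.** **Inputs from Sample Size.** "the number of predictors was set as 6"; f² = 0.10; "If α = 0.05, 1-β = 0.80, then the study requires enrollment of 143 participants"; "given a maximum anticipated dropout rate of 20%, a total sample size of 178 children with BCP and PWMLs will be needed".

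**The plan's own figure.** For the overall F test with 6 and N − 7 degrees of freedom and noncentrality 0.10 × N, the smallest N with power of at least 0.80 is 143 (power 0.801). Dropout: 143 / 0.80 = 178.75, against 178 stated. The calculation reproduces, apart from rounding down by one child.

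**Children per age band** (test cohort about one quarter; equal bands assumed).
- Full 20% dropout: 143 / 4 = 35.75; 35.75 / 3 = 11.9.
- No dropout: 178 / 4 = 44.5; 44.5 / 3 = 14.8.

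Unequal bands would leave some smaller.

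**Precision within a band** (Clopper-Pearson 95% interval).
- 9/12 correct (75%): 43% to 95%.
- 10/12 (83%): 52% to 98%.
- 12/15 (80%): 52% to 96%.

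For a difference between two bands of 12 at 75% accuracy, the approximate half-width is 1.96 × √(2 × 0.75 × 0.25 / 12) = 0.35, or 35 percentage points.

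**Power between two bands** (Fisher's exact test, two-sided 0.05; accuracies are assumptions).

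| Accuracies | 12 per band | 15 per band |
|---|---|---|
| 85% vs 70% | 0.05 | 0.08 |
| 85% vs 60% | 0.15 | 0.19 |
| 85% vs 50% | 0.30 | 0.37 |
| 85% vs 30% | 0.72 | 0.80 |

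Only a collapse in accuracy would be found reliably.

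**Possible dilution of a feature.** Let age explain a share s of a feature's within-group variance and be unrelated to outcome. A standardised difference d becomes d / √(1 − s) after adjustment, and the single-feature AUC is Φ(d / √2). The documents give no value for s, so a range is shown for d = 0.50 (unadjusted AUC 0.64).

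| s (assumed) | Adjusted d | AUC |
|---|---|---|
| 10% | 0.50 / √0.90 = 0.53 | 0.645 |
| 40% | 0.50 / √0.60 = 0.65 | 0.68 |
| 60% | 0.50 / √0.40 = 0.79 | 0.71 |

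The loss runs from negligible to material.

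**What the remedy could gain.** The training cohort is 143 × 0.75 = 107 children, about 36 per third of the age range. Power for 85% vs 60% would be 0.58 there, and 0.73 with all 143 (about 48 per third), against 0.15 with 12. These figures treat predictions as independent, which out-of-fold predictions are only approximately. They serve as a scale for comparison, not as a power claim for the continuous analysis.

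**Cost in sample size.** On the protocol's regression basis, with f² = 0.10 read as a partial effect, testing six MRI predictors over one added covariate still needs N = 143 (power 0.80).

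**The case against.** The best defence is that the plan already limits some age effects. Entry uses corrected age, lesion load is a proportion of each region, the atlas is brought into each child's own space, and streamline counts are corrected for distance and region volume. This stands for effects of brain size. It does not remove maturation effects, and the plan's own age check shows that its authors did not think the matter settled.

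An analysis plan might add age adjustment. But the article fixes the feature sets, the screen, the models and the use of age, so this is a stated choice and not an omitted detail. Its silence on covariates in the ComBat step is different: that may be left to a fuller document, and no point is made of it.

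Two stronger readings are tempting, and the documents support neither.

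- **That scan age confounds the models.** The protocol concedes only possible effects of age on imaging. Nothing links scan age to severity or to outcome, which is assessed in a set window of 48–60 months.
- **That the study fails because MRI's added value over clinical data cannot be shown.** The aims concern prediction from MRI and lesion and connectome methods; incremental value is not among them. The Introduction does say that "communication, cognition, and motor performance at an early age are critical for predicting future functional communication", but goes straight on to explain why standardised tests, parent-completed measures and classification systems are unreliable at this age. That is a reasoned ground for imaging-only models. What remains is a mismatch of rationale: the Introduction also names a model combining patient characteristics with MRI as the missing tool, and the plan does not build one.

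**Conclusion.** The point holds for the handling of age. A recorded baseline variable that the plan itself suspects of affecting its features is left out of screening and modelling. The only check on it uses about 12 to 15 children per band, with power of 0.15 to 0.19 for an assumed 25-point fall in accuracy. The band sizes assume equal bands and between 20% and no dropout.

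How much performance is lost is unknown. The range from 0.53 to 0.79 for an initial difference of 0.50 rests wholly on the assumed variance share. Noise from age is plausible on the plan's own statement; bias is conditional on a link that the document does not quantify. The primary aim does not fail, but it would be better served by an adjustment that costs almost nothing. A clinical comparator is an optional addition, not a required correction.

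**What to change.** In Development and Validation of Prediction Models:

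1. Include age at MRI in every model. Alternatively, residualise each feature on age before screening, with coefficients estimated in the training folds only. For the final model, estimate them in the whole training cohort and apply them unchanged to the test cohort.
2. Nest the two-sample screening within the folds, so that out-of-fold predictions are not optimistic.
3. Replace the three-band check with age at MRI as a continuous modifier of prediction error, reported with its confidence interval. Use nested out-of-fold predictions in the training cohort and hold-out predictions in the test cohort, reported separately or jointly with cohort as a term.
4. If bands are kept, make them non-overlapping and label them descriptive.

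Optional secondary analysis: prespecify one clinical-only model from variables already collected, and report the AUC difference for clinical plus MRI with its confidence interval. State that it will be imprecise. In about 36 test children the standard error of a single AUC of 0.80 is about 0.08 (17 impaired and 19 unimpaired, taking the 47% cited in Sample Size), and on the regression basis above the power for the MRI increment is about 0.20.

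The cost is somewhat more analysis work, mainly from nesting. No new data or children are needed. MRI's apparent performance may come out smaller.

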
### Confidentiality and Data Management

The original data will be kept confidential throughout the study and preserved by The Affiliated Hospital of Zunyi Medical University, China. The electronic data will be gathered at each site and supervised by the two specially trained investigators. The data will be stored in a secure computer, and only research staff will have access to the data. Unless required by law, none of the above information will be divulged. Anonymized study data will be published for scientific purposes.

### Trial Status

This trial is currently recruiting participants.

## Discussion

This study protocol reports the procedures for a prospective, multicenter, longitudinal cohort study that will establish an individual-based model for the prediction of communication impairment in children with BCP and PWMLs at school entry.

This study will have some potential strengths. Previous studies (Geytenbeek et al., 2015; Coleman et al., 2016; Choi et al., 2017; Laporta-Hoyos et al., 2018) have demonstrated that the type and severity of brain injury shown on MRI scans is associated with communication impairment. However, all these studies were retrospective in design and were performed to identify risk factors for communication impairment, and an individualized prediction model for communication is still lacking. Moreover, wide ranges of communication performance in the specified type or degree of injuries suggest the limited value of predicting communication outcomes based on quantitative and semiqualitative parameters (Geytenbeek et al., 2015; Coleman et al., 2016; Laporta-Hoyos et al., 2018). In this study, a large representative sample of children with BCP will be recruited, and the data will be collected prospectively using standardized neuroimaging protocols and outcome measures. An individual-based prediction model for communication ability will be developed based on quantitative MRI parameters. This model can provide information that can contribute to the determination of the appropriate time for intervention and guide decision-making. In addition, only a few articles (Geytenbeek et al., 2015; Coleman et al., 2016; Choi et al., 2017) have reported brain-communication relationships in children with CP, and neuroimaging characteristics identified as risk factors in these studies are quantitative and/or semiqualitative parameters. Hence, the neuroanatomic basis for communication impairment remains unclear (Vaillant et al., 2020). We will use voxel-based analyses to examine which regions are typically associated with communication impairment. Connectome-based analyses, a novel approach for identifying key connections for neurological function, will also be used to provide unique insights into communication deficits. In this light, it can be foreseen that the abovementioned methods would greatly help in the understanding of the neural basis of communication impairment in these children.

With the growing number of multisite neuroimaging studies, there is a great challenge in handling non-biological variance due to site-level factors, such as differences in MRI scanners and/or acquisition protocols. Such unwanted sources of variability and bias may mask true associations of interest and/or generate spurious findings. In this multisite neuroimaging study, we will use ComBat (Fortin et al., 2017, 2018), a well-established methodology for controlling unwanted variation induced by scanner and/or acquisition protocol differences, to remove site effects. Moreover, due to difficulties in obtaining neuroimaging data in children with CP (accompanied by multiple complications), our hospital will develop an individualized examination procedure for these children and extend it to other participating sites to ensure the feasibility of the process. During this period, translation of specialist knowledge and dissemination of research results into clinical practice will begin immediately via site investigators. The university affiliations across this study will provide opportunities to integrate research fronts and introduce this collaborative effort into undergraduate education. Knowledge translation will also target parents and/or guardians of children with CP to improve their quality of life.

This study will have several limitations. Given the multidimensional nature of communication, attempting to reduce communication skills to a single linear scale will be fraught with the problems of overlooking impairment-related data and important, informative developments (Potter, 2016; Nordberg, 2018). Therefore, the CFCS may not be able to capture the full scope of information necessary to evaluate cross-sectional performance and track the longitudinal development of communication ability. However, quantitative communication tests in the Chinese version for children with CP are scarce. The CFCS has been translated into different languages (Hidecker et al., 2011; Vander Zwart et al., 2016; Wang and Wei, 2017; Choi et al., 2018; Mutlu et al., 2018) and has often been used in multiple CP registries (Coleman et al., 2015; Hustad et al., 2016; Mei et al., 2016; Vander Zwart et al., 2016; Wang and Wei, 2017; Mutlu et al., 2018) worldwide. It shows good reliability and validity across different cultures and languages (including the Chinese version) and is quick and user friendly, making it ideally suited for multicenter trials. Thus, we will still consider CFCS as the primary outcome measure, and a search for precise scales in the Chinese version that enable quantitative evaluation of communication ability for these children will be continued. Functional MRI has great potential for characterizing typical development and detecting abnormalities early; however, it will not be included in our present study because of the poor ability of infants to tolerate MRI scanning (furthermore, after conventional and diffusion sequences, the evaluation time would be too long to include MRI examination). Finally, it should be noted that our study population is limited to children with BCP and PWMLs to reduce the heterogeneity in constructing more accurate predictive models. Thus, the prediction models constructed by this protocol will likely not be generalizable to other CP subtypes or BCP with other neuroimaging findings.

## Ethics Statement

The studies involving human participants were reviewed and approved by the Institutional Review Board of The Affiliated Hospital of Zunyi Medical University (KLL-2021-108). All participating centers approved this study protocol. Written informed consent form will be obtained from the legal parents/guardians of all participants.
